### Concomitant medications

#### Permitted

In this trial, patients taking only one kind of csDMARDs should be selected. CsDMARDs having been taken for more than 3 months with stable dose will be allowed and the dose cannot be changed during the trial. Patients who have taken NSAIDs and/or oral corticosteroid (less than 10 mg/day) with stable dose for at least 4 weeks will be permitted and any change of dose will be recorded. Notably, acetaminophen may be used if necessary (for patients with VAS for pain ≥6 cm) during the trial, and it will be recorded.

#### Prohibited

It includes medicines that can affect the primary outcome, such as 1) Chinese medicine with the same or similar function as KBXG, 2) corticosteroid injections, 3) Oral corticosteroid/NSAIDs administered for other diseases, and 4) bDMARDs, cell proliferation inhibitors, and/or immunosuppressants.

### Outcomes and measurements

#### Primary outcome

The primary outcomes are the change in DAS28-CRP and CDAI at every visit.

The DAS28-CRP is widely used as an indicator of RA disease activity and response to treatment, and clinical trials have used DAS28 to assess treatment effect (Gardiner et al., 2005; Jain et al., 2021; Zhang et al., 2022). A change of ≥1.2 score is considered clinically significant difference (Van Gestel et al., 1998). The DAS28-CRP is calculated as DAS28-CRP = 0.56*sqrt (TJC28) + 0.28*sqrt (SJC28) + 0.36*ln (CRP+1) + 0.014*VAS +0.96 (van Riel, 2014).

The CDAI is calculated as CDAI = TJC28 + SJC28 + overall disease activity on a 0–10 VAS completed by the patient + overall disease activity on a 0–10 VAS completed by the physician (Aletaha et al., 2005). High disease activity is defined as a CDAI >22, moderate activity as a CDAI >10 and ≤22, low activity as a CDAI >2.8 and ≤10, and remission as a CDAI ≤2.8.

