## Methods

### Trial design

This is a single-center, randomized, double-blind, parallel group, placebo-controlled clinical trial. The trial will be conducted in the Xiyuan Hospital of China Academy of Chinese Medical Sciences. A total of 90 eligible female participants will be randomized into the experimental group (KBXG) or the control group (placebo) with a 1:1 ratio. Two groups will continue their original treatment regimen during the trial. The duration of the intervention is 12 weeks, and follow-up is 12 weeks. Study visits will take place at baseline and at 4, 8, 12, 24 weeks. Every patient will be asked to visit within 3 days of the given time point. All participants will be required to sign the written informed consent before randomization. This protocol was compiled in line with the Standard Protocol Items: Recommendations for Interventional Trials (SPIRIT) Guidelines (Chan et al., 2013), which is presented in the Supplementary Material S1. The flowchart of this trial is presented in Figure 1.

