### Participant timeline

The schedule of enrollment, interventions, and assessments is as shown in Table 2.

**TABLE 2 T2:** A standard protocol items: recommendation for interventions for trials (SPIRIT).

	Study period						
	Enrollment	Allocation		Post-allocation			Follow up
Time point	- Day 3	Day 0	Week 0	Week 4	Week 8	Week 12	Week 24
Enrolment							
Eligibility screen	X						
Informed consent	X						
Allocation		X					
Interventions							
KBXG			X	X	X	X	
Placebo			X	X	X	X	
Assessments							
DAS28-CRP	X			X	X	X	X
CDAI			X	X	X	X	
ACR20/50/70			X	X	X	X	
TCM syndrome score			X	X	X	X	X
VAS			X	X	X	X	X
Average hands grip strength			X	X	X	X	X
HADS			X	X	X	X	X
L-BMD			X				X
US7			X			X	X
Consumption of concomitant medications	X		X	X	X	X	
ESR, CRP	X			X	X	X	X
Blood routine	X					X	X
Urine routine	X					X	X
Stool routine	X					X	X
Liver and kidney function	X					X	X
AEs			X	X	X	X	

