### Sample size

The sample size is calculated based on the primary endpoint (the changes in DAS28-CRP). According to the previous exploratory clinical trial (unpublished), the effect size of the treatment group was 83.9%, with a power of 0.9 and alpha of 0.05, a total of 68 female patients should be included to determine an increase of 15% in disease activity improvement between the KBXG and placebo groups. To account for a 20% loss to follow-up, at least 85 female patients will be required in this trial. Thus, a total of 90 female patients (45 female patients in each group) are planned to be enrolled.

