### Statistical methods

Data analysis will be completed using SPSS 23.0, according to the intention-to-treat analysis and the per-protocol analysis. Baseline analyses will be performed using analysis of variance or non-parametric tests for continuous variables, and chi-squared or Fisher’s exact tests for categorical variables, respectively. Changes from baseline to post-treatment in DAS28-CRP, CDAI, TCM syndrome scores, VAS, average hands grip strength, HADS, L-BDM and US7 will be analyzed. The results of the two groups will be analyzed using analysis of covariance with associated 95% confidence intervals. The rates of participants achieving good responses on ACR will be compared. A two-sided *p* value of < or = 0.05 is considered statistically significant. Multiple imputations will be used to handle any missing data. For safety, the incidence of AEs will be analyzed and compared. The details of each AEs will be analyzed.

Participants with poor adherence, compliance of experimental drug <80%, or those no longer receiving medication and undergoing testing during the study will be included in the intention-to-treat analysis and excluded from the per-protocol analysis. Multiple imputation will be used for missing data.

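### Two scores are primary at every visit with one unadjusted 0.05 and no success rule, so the false-positive rate could exceed 5%, to roughly 15–30% if any significant result counts

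*Protocol article*

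**What the plan says.** - Primary outcome section: "The primary outcomes are the change in DAS28-CRP and CDAI at every visit".
- Trial design: "Study visits will take place at baseline and at 4, 8, 12, 24 weeks". Treatment lasts 12 weeks, so the last visit falls 12 weeks after it ends.
- Participant timeline, Table 2: DAS28-CRP is marked at Weeks 4, 8, 12 and 24 after baseline. CDAI is marked at Weeks 0, 4, 8 and 12, and its Week 24 cell is empty.
- Sample size: "The sample size is calculated based on the primary endpoint (the changes in DAS28-CRP"). One endpoint is named, without a week, at an alpha of 0.05 and power of 0.9.
- Statistical methods: the outcomes are analysed as "Changes from baseline to post-treatment in DAS28-CRP, CDAI, TCM syndrome scores" and so on. The method is given as "The results of the two groups will be analyzed using analysis of covariance with associated 95% confidence intervals". A two-sided p "value of < or = 0.05 is considered statistically significant". Which week is meant by post-treatment is not said.

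The article gives no either/both rule for the two scores, no order of testing and no division of alpha.

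**The concern.** The Introduction says the trial is meant to confirm efficacy. A confirmatory claim needs one identifiable result, or a stated rule over several results, that decides whether the trial succeeded. Here primary status is spread over two scores and every visit, and each comparison faces the same 0.05.

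Without a rule, a significant DAS28-CRP result at Week 4 or a significant CDAI result at Week 8 could be reported as a positive primary outcome even if Week 12 shows nothing. The 5% that the reader takes from the plan would then not describe the claim being made.

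The outcome definition also fits poorly with two other parts of the article. The sample size rests on a single primary endpoint, and the schedule does not collect CDAI at one of the visits where it is declared primary.

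**Working it through.** **Inputs from the article.** Two scores; post-baseline visits at Weeks 4, 8, 12 and 24; two-sided alpha 0.05.

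**Inputs assumed.** The article gives no correlations between test statistics. I used 0.5–0.9 between DAS28-CRP and CDAI, which share both joint counts and a patient rating, and 0.3–0.8 between visits.

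**Number of primary contrasts.**
- By the text: 2 scores × 4 visits = 8.
- By Table 2: 4 for DAS28-CRP + 3 for CDAI = 7.

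**The plan's own figure.** One score at one visit, tested at 0.05, has a 5% error rate. The stated alpha is therefore correct for a single contrast, which is what the sample-size section assumes.

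**If any one significant result counts: ceiling under independence,** 1 − 0.95^k:
- k = 8: 1 − 0.95^8 = 33.7%
- k = 7: 1 − 0.95^7 = 30.2%
- k = 2 (both scores, one visit): 1 − 0.95^2 = 9.75%

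**The same rule with correlated tests.** I simulated null trials with normal test statistics and counted those with at least one |z| > 1.96. The correlation matrix is the 2 × 2 score matrix crossed with a 4 × 4 visit matrix with equal correlation between visits. The seven-contrast column drops CDAI at Week 24.

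| Between scores | Between visits | 8 contrasts | 7 contrasts |
|---|---|---|---|
| 0.5 | 0.3 | 30% | 27% |
| 0.6 | 0.5 | 26% | 24% |
| 0.7 | 0.5 | 25% | 23% |
| 0.9 | 0.8 | 16% | 15% |

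Letting the correlation decay with the distance between visits raises the top of the range only to about 31%.

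**Both scores at one post-treatment visit, either one sufficient.** 9.1% at correlation 0.5, 8.3% at 0.7 and 7.0% at 0.9.

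**If every contrast must be significant.** Below 1% when neither score is affected at any visit. An all-must-succeed rule cannot exceed 5% in any case.

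**After the fix.** DAS28-CRP at Week 12 is tested at 0.05. CDAI at Week 12 is tested at 0.05 only if the first test succeeds. The error rate over the two is at most 5% at the final analysis, because no claim is possible without passing the first test.

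**The alternative of splitting alpha, 0.025 per score.** Assume 34 per arm (68 in total) gives 90% power at 0.05. The implied standardised difference is (1.960 + 1.282) / √(34/2) = 0.786.
- Power at 0.025: Φ(0.786 × √17 − 2.241) = Φ(1.00) = 84%.
- Per arm for 90% power: 2 × (2.241 + 1.282)² / 0.786² ≈ 40.2, so 41, or 82 in total.
- With 20% loss: 82 / 0.80 = 102.5, so 103 patients, against 90 planned.

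The 0.786 is back-solved for this comparison only and does not stand in the article.

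**The case against.** The strongest reply is that the error rate depends on a success rule the article never states. The 0.05 in Statistical methods is a general threshold for all analyses, and no sentence says that any single significant contrast makes the trial positive. A reader might infer that the false-positive rate simply is some figure between 15% and 30%. The document does not support that: the rate runs from below 5% if all contrasts must succeed, through 7–9% for two scores at one visit, to 15–30% if any contrast suffices. This part of the reply stands, and the figures here are conditional for that reason.

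A reader might also infer that the outcome, sample-size and analysis sections define three different primary questions. That goes too far. Sizing a trial on one of two primary outcomes is common. The baseline to post-treatment sentence covers all continuous outcomes and can be read as one contrast per score. What remains is that the sample-size section speaks of one primary endpoint where the outcome section has two, and that no place names the deciding week.

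Two further extensions fail. The article plans both intention-to-treat and per-protocol analyses without ranking them, but that can be left to the analysis plan. It also plans an interim analysis of the primary outcome at 50% of recruitment, but does not say that efficacy would be declared there or at what threshold, so no inflation figure can be attached to it here.

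Finally, a multiplicity procedure may sit in an analysis plan that is not shown, and its absence from an article is no fault. That does not answer the point. The identity and timing of the primary endpoint are fixed in this article, and they are fixed as two scores at all visits. An analysis plan that chose one score and one week would contradict the article as written.

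**Conclusion.** The point holds in conditional form. The primary definition is badly fixed: two scores, all visits, an unadjusted 0.05, no deciding week and no either/both rule. It sits beside a sample size built on DAS28-CRP alone and a schedule without CDAI at Week 24.

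If any one significant result counts as success, the false-positive rate for the primary claim could reach roughly 15–30% over seven or eight contrasts, instead of 5%. If both scores are tested at one post-treatment visit and either suffices, it is about 7–9%. Both ranges rest on assumed correlations. Using seven contrasts instead of eight lowers the figures by about 1 to 3 percentage points and does not change the conclusion. Because the trial is presented as confirmatory, the definition should be corrected before unblinding; a choice made afterwards would not be credible.

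**What to change.** 1. Name one primary endpoint: change from baseline in DAS28-CRP at Week 12, the end of treatment and the outcome on which the trial was sized. Analyse it by the planned analysis of covariance with the baseline value as covariate.
2. Make change in CDAI at Week 12 the key secondary endpoint, tested at two-sided 0.05 only if DAS28-CRP at Week 12 is significant.
3. Describe the other scheduled visits of both scores as supportive, with estimates and confidence intervals and no claim of success attached.
4. Reconcile the outcome definition with Table 2: either CDAI is assessed at Week 24 or the wording that covers every visit is changed.

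The cost is wording, plus loss of primary status for CDAI and for the other visits. No patients or data are lost, and the planned 90 need not change on this account. Keeping both scores as co-equal primaries with alpha split in two would instead lower power from 90% to about 84%, or need about 103 patients, under the assumption shown in the working.

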#### Secondary outcomes

Secondary outcomes are the following:1) The rate of achieving ACR20, ACR50, ACR70 (Felson and LaValley, 2014). Measurement will be performed at every visit. Briefly, ACR20/ACR50/ACR70 is defined as a more than 20%/50%/70% improvement respectively in both tender joint count (TJC) and swollen joint count (SJC). Patients should simultaneously have a more than 20%/50%/70% improvement respectively in at least 3 items as follow: patient’s assessment of pain on a VAS, patient’s global assessment of disease activity, physician’s global assessment of disease activity, HAQ-DI and CRP level.2) Changes in TCM syndrome score. It will be evaluated based on the grading scales of RA symptoms required in the Guiding Principles of Clinical Research of New Chinese Medicine Treating RA (2002 Edition) issued by the National Medical Products Administration of China at every visit. The scores and details are presented in the Supplementary Material S4.3) Changes in VAS. Pain will be evaluated using a VAS at every visit according to a former study (Faiz, 2014).4) Changes in average hands grip strength. Measurement will be performed at every visit. The Jamar dynamometer is used to assess the hand grip strength (Higgins et al., 2018). For each strength test, three times of measurements should be done for each hand, and the mean score of both hands is recorded.5) Changes in HADS. Anxiety and depression will be evaluated at every visit according to a former study (Herrero et al., 2003).6) Changes in lumbar spine bone mineral density (L-BMD) to assess osteoporosis. Measurement will be performed at baseline and week 24.7) Changes in 7-joint ultrasound score (US7). Measurement will be performed at baseline and week 12, 24. It determines the severity of synovitis, synovial hyperplasia and bone erosion of 7 joints through color Doppler ultrasound semi-quantitative assessment (Backhaus et al., 2009). The scores and details are presented in the Supplementary Material S5.8) Consumption of concomitant medications. We will record any changes in the dose of NSAIDs or oral corticosteroids in the case report form (CRF). The drug name, total daily dose, and single dose will be record at every visit.

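### CDAI (a primary outcome), ACR response and concomitant medication are set for every visit in the text, but Table 2 leaves all three blank at Week 24, where it does schedule DAS28-CRP

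*Protocol article*

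**What the plan says.** Trial design lists the visits: "Study visits will take place at baseline and at 4, 8, 12, 24 weeks". It also gives the periods: "The duration of the intervention is 12 weeks, and follow-up is 12 weeks". Week 24 is therefore a study visit, 12 weeks after treatment ends.

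Primary outcome: "The primary outcomes are the change in DAS28-CRP and CDAI at every visit". The same section defines CDAI as the sum of the 28-joint tender and swollen counts, the patient's global rating and the physician's global rating.

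Secondary outcomes has ACR20/50/70 measured at every visit. For concomitant medication it says: "The drug name, total daily dose, and single dose will be record at every visit". The section on permitted concomitant medications adds that dose changes of NSAIDs or oral corticosteroids, and use of acetaminophen, are to be recorded.

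Participant timeline: "The schedule of enrollment, interventions, and assessments is as shown in Table 2". In that table the ACR row reads "ACR20/50/70 X X X X" (Weeks 0, 4, 8 and 12), and the CDAI row has the same four marks. The medication row reads "Consumption of concomitant medications X X X X X" (Day -3 and Weeks 0, 4, 8 and 12). The DAS28-CRP row reads "DAS28-CRP X X X X X" (Day -3 and Weeks 4, 8, 12 and 24).

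**The concern.** The two primary outcomes are given the same timing in the text but different timing in the schedule, and the article does not explain the difference. A site working from Table 2 would see the patient at Week 24, collect what DAS28-CRP needs, and not ask the physician for a global rating. That rating cannot be recovered afterwards, so a primary outcome at one stated visit would be lost.

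The medication row matters for a different reason. Week 24 DAS28-CRP is measured after 12 weeks off study treatment, when background NSAID or corticosteroid doses may have changed. If the visit does not prompt a medication record, a difference between groups in DAS28-CRP at Week 24, or its absence, is harder to interpret.

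**Working it through.** No sample size, power or alpha enters this point, and the plan states no figure to reproduce. The check sets text against table.

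**1. Is the blank real, or a text-extraction shift?** Table 2 has seven time columns: Day -3, Day 0, and Weeks 0, 4, 8, 12 and 24. Mapping each row to these columns by its tab positions gives:

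| Row | Marked at | Week 24 |
|---|---|---|
| DAS28-CRP | Day -3, Weeks 4, 8, 12, 24 | yes |
| ESR, CRP | Day -3, Weeks 4, 8, 12, 24 | yes |
| TCM syndrome score | Weeks 0, 4, 8, 12, 24 | yes |
| VAS | Weeks 0, 4, 8, 12, 24 | yes |
| CDAI | Weeks 0, 4, 8, 12 | **no** |
| ACR20/50/70 | Weeks 0, 4, 8, 12 | **no** |
| Concomitant medication | Day -3, Weeks 0, 4, 8, 12 | **no** |

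A count supports this without relying on alignment. Baseline plus four later visits needs five marks. TCM score, VAS, grip strength and HADS, also set for every visit, each have five. CDAI and ACR have four, so they are one short however the columns fall. The medication row has five marks, but one is at Day -3 in addition to Week 0, and its last mark is at Week 12.

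**2. How much of the primary outcome is affected?** Read literally, the text gives 2 outcomes × 4 post-baseline visits = 8 outcome-by-visit results. Table 2 schedules 4 (DAS28-CRP) + 3 (CDAI) = 7. The one left over is CDAI at Week 24. This count is mine; the article does not list a set of eight.

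**3. Can CDAI at Week 24 be built from what is marked?** DAS28-CRP supplies the two joint counts. It also supplies the patient's global rating if its VAS term is that rating; the article says only VAS. The physician's global is in no row marked at Week 24. One of the four terms is missing, so CDAI cannot be computed.

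**4. Can ACR response at Week 24 be built?** The article requires improvement in both joint counts and in at least 3 of 5 items: pain VAS, patient's global, physician's global, HAQ-DI and CRP. Assume that the DAS28-CRP joint counts serve for ACR and that its VAS is the patient's global. Then three items are available (pain VAS, patient's global, CRP) and two are not (physician's global, HAQ-DI). Let *k* be the number of available items that improve:

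- Either joint count fails: non-responder.
- Joint counts pass, *k* = 0: at most 0 + 2 = 2 items, non-responder.
- Joint counts pass, *k* = 3: responder.
- Joint counts pass, *k* = 1 or 2: the total lies between 1 and 3, or between 2 and 4, so status is undetermined.

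If the DAS28-CRP VAS is not the patient's global, only two items are available and three are not. Totals then run from 0 to 3, 1 to 4, or 2 to 5 for *k* = 0, 1 or 2. Each range spans the threshold of 3, so every patient whose joint counts pass is undetermined. The documents give no figures from which to estimate the share of patients in either case.

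**5. How many patients?** Up to 90 are randomised. With the article's own 20% allowance for loss, 90 × 0.80 = 72 would be expected at Week 24.

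**The case against.** The strongest reply is that nothing in the article makes Table 2 override the text. The table also departs from the text on safety laboratory tests: Safety assessment gives Weeks 4, 8 and 12 after enrollment, while the table marks Weeks 12 and 24. The table may therefore be the faulty part, and the case report form and full protocol are not shown. This stands. It makes the consequences conditional, but it leaves the contradiction in place.

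A second reply is that Statistical methods speaks of change from baseline to post-treatment, and Table 2 labels Week 24 as follow-up. If the analysis is at Week 12, the CDAI data it needs are fully scheduled. That limits the damage. It does not explain why the primary outcome is stated for every visit, or why DAS28-CRP is scheduled at Week 24 and CDAI is not.

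Some stronger readings are tempting, and the documents do not support them:

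- *A reader might infer that follow-up medication changes will go unrecorded.* The text says they will be recorded. What is missing is the mark in the schedule that would prompt it.
- *A reader might infer that all Week 24 ACR data are lost.* Status can be settled for some patients from items that are collected, as shown in the working.
- *A reader might infer that the whole of Week 24 CDAI would be filled in by multiple imputation.* The article applies imputation to missing data. It does not say that an assessment never scheduled counts as missing.

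**Conclusion.** The text and Table 2 contradict each other at Week 24 for CDAI, ACR20/50/70 and concomitant medication, and should be reconciled. If sites follow the table:

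- CDAI at Week 24 cannot be computed for any attending patient.
- ACR response at Week 24 is undetermined for a share of patients that the documents do not allow one to estimate.
- Interpretation of Week 24 DAS28-CRP is weakened, because the visit does not prompt a medication record.

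It would be wrong to conclude that a primary outcome has no data. CDAI is scheduled at Weeks 0, 4, 8 and 12, which covers the whole treatment period, and the sample size rests on DAS28-CRP, which is scheduled at Week 24. The point is of moderate weight: it is cheap to correct now, but a physician's rating not taken at the visit cannot be recovered later.

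**What to change.** Reconcile the text and Table 2, and check the case report form against both, before Week 24 visits take place. There are two ways to do it:

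1. Add Week 24 marks for CDAI (naming the physician's global) and for the ACR components (naming HAQ-DI and the physician's global).
2. Limit CDAI and ACR in Primary outcome and Secondary outcomes to Weeks 4, 8 and 12, and state that they are neither analysed nor imputed at Week 24.

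In either case, mark concomitant-medication recording at Week 24, as the text already promises. It would also help to say whether the VAS in the DAS28-CRP formula is the patient's global rating.

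The first option costs a few minutes per patient at a visit that already takes place. The second costs a text edit and gives up the Week 24 comparison on CDAI and ACR.
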